**Figure 1 F1:**
[figure not shown]
Consort flow diagram.

### Ethics approval and consent to participate

2.2

This study will be conducted in accordance with the principles of the Declaration of Helsinki for Clinical Research.^[13]^ The trial protocol has been approved by the Research Ethics Committee of Longhua Hospital Affiliated to Shanghai University of Traditional Chinese Medicine (No. 2019LCSY015). All participants will be given sufficient time to make a decision to provide written informed consent prior to the study.^[14,15]^ The protocol has been registered in the Chinese Clinical Trial Registry (ID: ChiCTR1900021825).

### Intervention

2.3

All patients will be treated by Shi-style lumbar manipulation combined with Daoyin therapy or mechanical lumbar traction. The patients in the treatment group will undergo Shi-style lumbar manipulation for 20 minutes every other day (3 times a week) for 4 weeks. They will also undergo Daoyin therapy of the muscle and bone once every other day for 6 months. If the patient has a visual analog scale (VAS) score of >7, analgesics may be allowed. All treatments and examinations will be free of charge to improve patients the compliance with the intervention plan. Analgesics will be allowed during the trial, but the patients will be required to record the medications taken.

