## Method/design

2

The purpose of this prospective randomized controlled clinical trial is to investigate whether Shi-style spine manipulation combined with Daoyin therapy can lead to improvements in middle-aged and elderly patients with LDH. The study will be conducted in the Department of Orthopaedics, Longhua Hospital, Shanghai University of Traditional Chinese Medicine. The principal investigator will be responsible for the entire project, including organization of the steering committee meetings. An independent steering committee will be responsible for participant safety, meetings, participant recruitment, and quality control. The coordination center will be responsible for communicating protocol modifications and providing materials. The trial will involve 4 weeks of treatment and 6 months of follow-up. After randomization, the patients will receive one course of treatment within 4 weeks. The results will be evaluated at baseline and at weeks 2, 4, 12, and 24.

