### Mechanical lumbar traction

2.6

Patients with pelvic traction lie supine on the traction bed, bend the hips and knees, place both feet on the bed, and keep waist attach to the bed. For the patient whose lumbar curvature uncurls or whose lumbar muscle is obviously tense, traction therapies should place a thin pillow approximately 1.5 cm high under his lower back of the waist. Traction posture is body bent at hips and knees. Traction weight is equal to 25% to 30% patients weight for the first time, 2 kg weight increased each time, until the traction weight reach at 40% to 60% of patients weight. The specific standard should be based on patients tolerance. Therapist uses intermittent traction method, lasts for 40 seconds, pauses for 10 seconds, 20 minutes each time, once every other day, 3 times a week, 4 weeks in all.

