### Safety assessment

2.8

The project director will supervise the data collection process to assure the safety of the participants. At each visit, the participants will be required to stay in the hospital for 30 minutes after the treatment and will be asked about any adverse effects that may indicate acute adverse reactions during the study period (e.g., lower limb paralysis or cauda equina syndrome). All adverse effects will be recorded at each visit during the treatment period.

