### Data collection and monitoring

2.12

This is a 24-week clinical trial in which the participants will undergo the research intervention for 4 weeks with a 24-week follow-up. The primary outcome measures will be assessed at 5 time points (at baseline and at weeks 2, 4, 12, and 24), the secondary outcome measures will be assessed at 2 time points (at baseline and at week 24), and safety will be assessed at 6 time points (at baseline and at weeks 1, 2, 4, 12, and 24). All results will be independently documented by 2 investigators using EpiData version 3.1 (EpiData Association, Odense, Denmark), and differences will be resolved through discussion with a third investigator. The Longhua Hospital Affiliated to Shanghai University of Traditional Chinese Medicine will be responsible for monitoring and quality control.

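### Section 2.3 runs Daoyin for 6 months in one arm, but sections 2 and 2.12 end treatment at 4 weeks, so the meaning of the week 12, week 24 and imaging comparisons is unsettled

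*Protocol article*

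**What the plan says.** Section 2.3 gives the treatment arm two components of different length. Manipulation is set as "Shi-style lumbar manipulation for 20 minutes every other day (3 times a week) for 4 weeks". The same section then adds: "They will also undergo Daoyin therapy of the muscle and bone once every other day for 6 months".

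Two other sections describe a single 4-week treatment phase. Section 2 states: "The trial will involve 4 weeks of treatment and 6 months of follow-up". It adds that after randomization "the patients will receive one course of treatment within 4 weeks". Section 2.12 states that "the participants will undergo the research intervention for 4 weeks with a 24-week follow-up".

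The control arm is described in section 2.6: traction is given "20 minutes each time, once every other day, 3 times a week, 4 weeks in all". No later study treatment for controls is described.

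Section 2.12 places the primary outcomes (VAS, PPT, ODI) at baseline and weeks 2, 4, 12 and 24. The imaging outcomes are at baseline and week 24 only. Safety is assessed at baseline and weeks 1, 2, 4, 12 and 24. Section 2.8 says: "All adverse effects will be recorded at each visit during the treatment period".

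**The concern.** Daoyin is half of the treatment under test. If it continues for 6 months, the experimental treatment does not stop at week 4, and sections 2 and 2.12 misdescribe the trial. If it does stop at week 4, section 2.3 is wrong. The text does not say which.

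The choice changes what half of the post-baseline visits estimate. If both arms finish at week 4, weeks 12 and 24 show whether any difference lasts after treatment. If Daoyin continues, the same visits compare patients still exercising under the protocol with patients whose assigned treatment ended 8 or 20 weeks earlier. A reader told that this period is follow-up would take a week-24 difference as a durable effect of a 4-week course. The imaging outcomes are the most exposed, because they have no post-baseline measurement before week 24.

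**Working it through.** The protocol states no session count or exposure share, so there is no figure of its own to reproduce. The check sets the statements side by side and counts exposure.

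**Two readings**

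| Point | Section 2.3 governs | Sections 2 and 2.12 govern |
|---|---|---|
| Daoyin ends | about 6 months | week 4 |
| Traction ends (2.6) | week 4 | week 4 |
| Weeks 2 and 4 | both arms on treatment | both arms on treatment |
| Weeks 12 and 24 | Daoyin against no further described study treatment | both arms off treatment |
| Imaging at week 24 | as weeks 12 and 24 | as weeks 12 and 24 |

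**Exposure if section 2.3 governs** (weeks counted from the start of treatment)

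- Weeks with assigned treatment in one arm only: 24 − 4 = 20. Share: 20 / 24 = 83%.
- Daoyin on strict alternate days: 24 weeks = 168 days, 168 / 2 = 84 sessions. The first 4 weeks = 28 days, 28 / 2 = 14 sessions. After week 4: 84 − 14 = 70, and 70 / 84 = 83%.
- For manipulation and traction, the protocol equates every other day with three times a week. On that usage Daoyin has 3 × 24 = 72 sessions, 3 × 4 = 12 of them by week 4, so 60 after week 4, and 60 / 72 = 83%.
- Traction: 3 × 4 = 12 sessions, none after week 4.
- If 6 months is taken as 26 weeks (182 days), the one-arm share of that period is (182 − 28) / 182 = 85%.

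**Outcomes affected**

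- Primary outcomes: weeks 12 and 24 are 2 of the 4 post-baseline visits, for each of three outcomes.
- Imaging outcomes: all of them, since the only post-baseline measurement is at week 24.

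**Does anything else settle the length?** No. The 2018 pilot in section 2.9 used an 8-week treatment, which matches neither figure.

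**Safety wording.** Section 2.8 ties recording to the treatment period, which is 28 days or about 182 days depending on the section. Section 2.12 schedules safety to week 24 under either reading. The two agree if the treatment period is 6 months; if it is 4 weeks, section 2.8 stops before the week 12 and week 24 assessments.

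**The case against.** The strongest reply is that unequal course length is not an error in itself. The discussion describes a comparison of two packages and presents Daoyin as exercise led by the patient, partly to prevent recurrence. Section 2.3 gives the two durations in consecutive sentences, which suggests intent. The trial may be a 4-week practitioner-delivered course in both arms, with self-directed exercise continuing in one. Comparing those strategies at week 24 is legitimate. This stands, and it is why the point is not that the longer Daoyin course is a mistake. It does not remove the contradiction: sections 2 and 2.12 still describe 4 weeks of treatment and then follow-up, which is a different comparison.

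A reader might also infer several stronger things that the document does not support:

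- *That the adverse-event window is wholly open.* Section 2.12 lists safety at weeks 12 and 24 without restriction by arm, and section 2.8 also asks about acute reactions over the study period. One phrase is out of line.
- *That 20 weeks of exercise go unmonitored.* This mixes the two readings: if treatment including Daoyin ends at week 4, no assigned exercise follows; if Daoyin runs on, the treatment period can cover it.
- *That early and late visits are pooled.* Section 2.13 plans a repeated-measures analysis of variance across time points, which does not merge visits.
- *That a late difference would reflect only exercise against nothing.* The treatment arm also had manipulation, analgesics are allowed, and the introduction says controls are mainly treated with traction. The accurate description is no further described study treatment.
- *That week 4 should become the primary time point.* Week 24 is equally defensible for a comparison of strategies, a change during recruitment is substantive, and it would not help imaging.

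**Conclusion.** The protocol is wrong as written. Section 2.3 conflicts with sections 2 and 2.12 on how long the experimental treatment lasts, so the text does not fix whether weeks 12 and 24 and all imaging are on-treatment or post-treatment comparisons. If section 2.3 governs, 83% of the 24 weeks have assigned study treatment in one arm only, and no result at those visits can be read as a lasting effect of a 4-week course. If sections 2 and 2.12 govern, that imbalance disappears and section 2.3 needs correcting. Which duration is right is for the investigators.

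This rests on two assumptions: that weeks are counted from the start of treatment, and that controls receive no study treatment after traction beyond what the article describes. The session counts depend on how every other day is read; the 83% share does not. The safety wording is a minor inconsistency.

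**What to change.** 1. Reconcile sections 2, 2.3 and 2.12 on the duration of Daoyin, and use the same statement in all three.
2. If Daoyin continues past week 4, describe weeks 12 and 24 and the imaging outcomes as a continuing-Daoyin strategy compared with a completed 4-week traction course, stop calling that period post-treatment follow-up, and limit the conclusions accordingly. If Daoyin ends at week 4, the existing follow-up description can stand once section 2.3 is corrected.
3. As a minor alignment, replace the treatment-period limit in section 2.8, and the matching sentence in the abstract, with adverse-event recording in both arms through week 24, as section 2.12 already schedules.

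The cost is wording: no visits, measurements or patients are added. The downside, if Daoyin continues, is that the week-24 and imaging results carry a narrower claim.

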### Shi-style spinal balance manipulation

2.4

#### Tendon soothing (Fig. 2a–c)

2.4.1

##### Rubbing method

2.4.1.1

The palm surface is used to make a straight or circular rhythmic movement on the waist and back for 2 minutes.

**Figure 2 F2:**
[figure not shown]
The Shi-style lumbar Balance manipulations include three steps and nine methods, the first step is Tendon soothing, Contains Rubbing, Kneading and Rolling methods (2a-c). The Second step is Osteopathic manipulation, Contains Extraction and extension, Lumbar flexion methods, Tilt (2d-f). The third step is Channel dredging, Contains Point, Shake, Pat methods (2g-i).

##### Kneading method

2.4.1.2

With one hand or 2 hands overlapping, the root of the palm is placed on the patients waist and back, and the practitioner presses and kneads along the midline and sides of the spine, hips, thighs, and back of the calves for 2 minutes.

##### Rolling method

2.4.1.3

The ulnar side of the palm (half-fist shape) is rolled on the patients waist and back, moving from the waist to the hips, thighs, and calf muscles for 2 minutes.

#### Osteopathic manipulation (Fig. 2d–f)

2.4.2

##### Extraction and extension

2.4.2.1

The patient is placed in the prone position. The physician stands on the left side of the patient, holding the patients knee joint with his or her right hand, holding the patients waist with his or her left hand, lifting the patients knee joint with his or her right hand, and pressing the waist vertically with his or her left hand; this process is repeated 3 to 5 times.

##### Lumbar flexion

2.4.2.2

The patient is placed in the supine position with the hips and knees flexed and the front of the thighs touching the abdomen. The physician stands on the right side of the patient, holding the patients legs with his or her left hand and lifting the patients hips with his or her right hand, thus extremely flexing the lumbar spine; this process is repeated 3 to 5 times.

##### Tilt

2.4.2.3

The patient lies on the right side first, with the right lower limb straight, the left lower limb flexed with hip and knee bent, the right hand straightened, the left hand flexed with the elbows on the waist, and the head lifted back later. The doctor stands on the right side of the patient, presses the patients left shoulder with his left hand and pushes backwards, and presses the right elbow to press the patients left iliac part and twists forward. Then let the patient turn over and repeat the above diagonal wrench method.

#### Collateral dredging (Fig. 2g–i)

2.4.3

##### Point method

2.4.3.1

The elbow joint is used to press the erector spinae muscles and sacroiliac muscles on both sides of the lumbar spine, and the thumbs are used to press the hips, thighs, posterior abdominal muscles, and calves. The pressure is held for 2 minutes.

##### Shake method

2.4.3.2

The patients ankles are held with both hands, and small, continuous upward and downward shaking movements are made with slight force. This is continued for 2 minutes.

##### Pat method

2.4.3.3

The palms or ulnar sides of the hands are used to pat the muscles on the back, hips, thighs, and back of the calf for 2 minutes.

### Guidance (Daoyin) for muscle and bone

2.5

#### *Leg lifts* (Fig. 3a1–4)

2.5.1

The patient lies on his or her back with the legs on both sides of the body or cross your hands in the back of your head. The left lower limb is lifted straight up to about 60° and maintained in this position for 5 seconds; it is then slowly lowered to the ground, and the process is repeated on the other side. Both lower limbs are then simultaneously lifted to about 30° and held in this position for 5 seconds; they are then slowly raised to 60° and held for 5 seconds. This process is repeated 5 times.

**Figure 3 F3:**
[figure not shown]
Guidance (Daoyin) for Muscle and Bone Contains four methods: Leg lifts (A1-4), Arch bridge (B1-4), Swallow exercise (C1-4), Stretching (D1-4).

#### *Arch bridge* (Fig. 3b1–4)

2.5.2

The patient is placed in the supine position. He or she flexes the hips and bends the knees, embracing the left knee with both hands and moving the left knee close to the torso; this position is held for 5 seconds. The same process is repeated on the contralateral side for a total of 5 times. Next, the knee is flexed to 90°, bilateral heel and shoulder three-point support, as far as possible to straighten the buttocks and maintain for 5 seconds, a total of 5 groups of practice.

#### Swallow exercise (Fig. 3c1–4)

2.5.3

The patient lies on his or her back with the elbows flexed on both sides of the body and the neck relaxed. The left lower limb is slowly lifted, keeping the thigh off the ground and maintaining this position for 3 seconds. The process is then repeated on the other side, and a total of 5 trials are performed. Extend the left hand with the head back and lift the upper body; this position is maintained for 3 seconds, and the process is repeated 5 times. Next, the hands are placed straight on both sides of the head, tilt back the head and lift the upper body while the legs are extended straight and lifted up; this position is maintained for 3 seconds and the process is repeated 5 times.

#### *Stretching* (Fig. 3d1–4)

2.5.4

For abdominal stretching, the patient is placed in the prone position with the elbows flexed on both sides of the body in line with the shoulders, and the neck is relaxed. Both upper limbs are then slowly straightened, and this position is held for 15 seconds. For back stretching, abdomen sticking out of the front of thighs and hips touching heels for 15 seconds. For hip stretching, the patient kneels on 1 knee with the knee flexed to 90°, the thighs and body at a 90° angle, and the back straight; this position is held for 15 seconds. Finally, for waist stretching, the patient is placed in the supine position, the knee joint is flexed to 90° and turned to one side, keeping the shoulders and hips away from the ground. The patient then holds the outside of the thigh against the ground for 15 seconds.

### Mechanical lumbar traction

2.6

Patients with pelvic traction lie supine on the traction bed, bend the hips and knees, place both feet on the bed, and keep waist attach to the bed. For the patient whose lumbar curvature uncurls or whose lumbar muscle is obviously tense, traction therapies should place a thin pillow approximately 1.5 cm high under his lower back of the waist. Traction posture is body bent at hips and knees. Traction weight is equal to 25% to 30% patients weight for the first time, 2 kg weight increased each time, until the traction weight reach at 40% to 60% of patients weight. The specific standard should be based on patients tolerance. Therapist uses intermittent traction method, lasts for 40 seconds, pauses for 10 seconds, 20 minutes each time, once every other day, 3 times a week, 4 weeks in all.

### Outcome measures

2.7

#### Primary outcome measures

2.7.1

Because pain is the most common symptom in patients with LDH, we chose the VAS score as one of the primary outcome measures for evaluating low back and leg pain. The VAS is a reliable and effective pain measurement tool. It is a 100-mm horizontal line showing “no pain” on the left (score of 0) and “ most severe pain possible” on the right (score of 10). In this study, the patients will use the VAS to indicate their current pain level at rest and during the most intense exercise,^[16]^ and the VAS score will thus be determined.

The pressure pain threshold (PPT) will also be measured. The PPT refers to the pressure applied when the patient feels pain in a certain area, and it is measured in units of kg/cm^2^. More severe pain is associated with a smaller PPT; conversely, less severe pain is associated with a larger PPT. In this study, a hand-held pain meter will be used to measure the PPT in the painful area of the neck. The patient will be placed in the prone position, and the pain meter will be pressed down onto the skin within the area of measurement. When the patient feels pain, the application of pressure will be stopped, and the screen of the pain meter will show the PPT.

The final primary outcome measure will be the Oswestry disability index (ODI). The ODI consists of 2 parts and a total of 10 evaluation items. The first part assesses low back pain and related symptoms (intensity of pain, concentration, and sleep), and the second part assesses activities of daily living (personal care, heavy lifting, reading, working, driving, and entertainment). The ODI is filled out by the patients according to their own conditions. Each item has a minimum score of 0 and a maximum score of 5, with higher scores indicating more serious dysfunction.

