### Statistical analyses

2.13

Trained statisticians will use the intentionality approach for validity assessment and safety analysis. The final outcome observation method will be applied to deal with missing values. All statistical analyses will be performed using SPSS version 22.0 (IBM Corp.). Before randomization, the patients baseline characteristics will be collected as descriptive statistics, including sex, age, body mass index, duration of symptoms, and degree of LDH. The data analysis of the primary outcome will be based on the per-protocol population as a supportive analysis. The mean, standard deviation, median, quartiles, and interquartile ranges will be calculated for continuous variables, and the frequency will be calculated for categorical variables. Continuous variables with a normal distribution will be calculated by the independent-samples Student *t* test and presented as mean with standard deviation; otherwise, the data will be analyzed using non-parametric tests and expressed as median with range.

Categorical variables will be expressed as number (%) and analyzed by the χ^2^ test or Fisher exact test. Repeated-measures analysis of variance will be used to analyze the changes in the VAS score, PPT, and ODI score at different time points (baseline and weeks 1, 2, 4, 12, and 24). An independent-samples *t* test will be used to analyze the changes in lumbar lordosis, lumbar vertebral angle, tilt angle of the first thoracic vertebra line, PI, PT, SS, and LM at baseline and 24 weeks. A *P* value of <.05 will be defined as statistically significant, and two-sided 90% confidence intervals will be calculated. Missing data will be input with the last observed response carried forward for all measures using the “last-value-carried-forward” principle.

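### VAS, PPT and ODI are all primary at P < .05 with no lead outcome, order or success rule, so a claim resting on any one carries about a 10–14% false-positive chance, not 5%

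*Protocol article*

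**What the plan says.** All references are to the protocol article.

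- **Primary outcomes (2.7.1).** Three measures stand under this heading. On pain: "we chose the VAS score as one of the primary outcome measures for evaluating low back and leg pain". Next: "The pressure pain threshold (PPT) will also be measured". Last: "The final primary outcome measure will be the Oswestry disability index (ODI".
- **VAS ratings (2.7.1).** "the patients will use the VAS to indicate their current pain level at rest and during the most intense exercise". The text then speaks of a single VAS score without saying which rating it is or how the two combine.
- **Visits (2.12).** "The primary outcome measures will be assessed at 5 time points (at baseline and at weeks 2, 4, 12, and 24". That is four post-baseline visits, none marked as primary. Section 2.13 lists the time points as "baseline and weeks 1, 2, 4, 12, and 24", which adds week 1.
- **Analysis (2.13).** "Repeated-measures analysis of variance will be used to analyze the changes in the VAS score, PPT, and ODI score at different time points". The effect to be tested (group, time or their interaction) is not named. P < .05 is the only significance criterion. The intervals are two-sided 90%.
- **Sample size (2.9).** This rests on one binary endpoint, improvement in the neck disability index, and a non-inferiority test.

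**The concern.** When three outcomes share primary status and one threshold, and nothing says whether all must succeed or one is enough, significance on any of them can be reported as meeting a primary outcome. The 5% threshold then no longer describes the chance of a false claim for the trial. The two VAS ratings add a further choice, and so do the unnamed effect and visit.

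Two features raise the stakes. Section 2.11 says that patients will not be blinded (although the same section also lists participants among those blinded), and VAS and ODI are self-rated. The abstract also promises convincing evidence of efficacy.

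**Working it through.** **The plan's own figure.** The article states no overall error rate. Its only error calculation is the sample size in 2.9, which reproduces:
- p = (0.920 + 0.866)/2 = 0.893.
- 2 × (1.645 + 0.842)² = 12.365, which is a one-sided 5% constant.
- n = 12.365 × 0.893 × 0.107 / 0.2² = 29.54 per group.

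This is one test of one endpoint. It makes no allowance for several primaries, and because that endpoint is none of the three, it does not identify a lead outcome either.

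**Inputs.** Three primaries (2.7.1), or four scores if VAS at rest and on exercise are tested apart. Four post-baseline visits (2.12). Each test at 0.05 (2.13). The correlations are assumptions, since the article gives none, and are varied from 0 to 0.8.

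**Method.** For k independent tests, the chance of at least one false positive is 1 − 0.95^k. For correlated tests, two-sided normal statistics were simulated (400,000 draws, equal correlation).

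**One test per outcome or score, the reading closest to 2.13:**

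| Tests | Independent | Correlation 0.5 | Correlation 0.8 |
|---|---|---|---|
| 3 outcomes | 1 − 0.95³ = 14.3% | 12.5–12.6% | 9.7–9.9% |
| 4 scores (two VAS ratings) | 1 − 0.95⁴ = 18.5% | 15.5% | 11.4% |

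Where a range is shown, it spans repeat runs.

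**Three outcomes, each of four visits also tested (12 tests), for comparison only:**

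| Correlation between outcomes / between visits | At least one false positive |
|---|---|
| Independent | 1 − 0.95¹² = 46.0% |
| 0.5 / 0.6 | 33% |
| 0.5 / 0.7 | 30% |
| 0.8 / 0.8 | 21% |

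**Direction.** These rates count a false difference in either direction. Counting only results that favour the treatment group, three independent tests give 1 − 0.975³ = 7.3% against a nominal 2.5%, so the inflation is again about threefold. If each test were a one-sided 5% test, as the sample size implies, the independent figure would again be 14.3%.

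**After repair.** One named test, or a fixed order with each test at 5%, holds 5%. Bonferroni at 0.05/3 = 0.0167 gives 1 − (1 − 0.0167)³ = 4.9% if independent.

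**The case against.** **One model per outcome.** The named method is a repeated-measures ANOVA for each outcome, which pools the visits. A reader might infer from the visit schedule that every outcome is compared at weeks 2, 4, 12 and 24, giving a dozen or more tests and an error of 33–46%. The article does not support that: 2.12 says only when the outcomes are measured, and 2.13 specifies no visit-by-visit tests of the primaries. This objection stands and sets the size of the point. Visit-wise claims remain possible only because no effect or visit is named.

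**No success rule is fixed at all.** P < .05 defines significance, not trial success. An all-must-win rule would not inflate the error. That is right, so the figures are conditional on an any-one-suffices reading. But no all-must-win rule appears.

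**Detail for an analysis plan.** Multiplicity handling may be left to a document not shown. That is fair for the detail. But this article itself fixes three primaries and a single threshold for all of them, and that combination is what needs repair.

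**VAS scores.** Two ratings, rest and exercise, are certain. Separate back and leg scores might be inferred from the mention of both sites, but the article does not state them, and they are not counted here.

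**Non-inferiority.** Section 2.9 announces a non-inferiority test, and the 90% intervals in 2.13 fit a one-sided 5% test. A repair that simply imposed two-sided 5% superiority tests would change the framework. This stands and is reflected in the fix.

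**Conclusion.** The point holds at moderate size. With one test per outcome, the chance of at least one false-positive primary result is 14.3% if the outcomes are independent, about 12.5% at correlation 0.5 and about 10% at 0.8: two to three times 5%. If the two VAS ratings are tested separately, it is about 11–16% at correlations of 0.8 to 0.5. It would be about 21–46% only if each of four visits were tested as well.

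This rests on two assumptions: that success on any one primary would support a claim, which the article neither states nor excludes, and the correlations. It should be corrected before any comparative look at the data. It does not call the design or the sample size arithmetic into question.

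**What to change.** Before any comparative look at the data:

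1. Name one VAS score and, for each primary, one between-group contrast: either one visit or the group-by-time effect.
2. Test in a fixed order, for example VAS, then ODI, then PPT, each at the plan's significance level, stopping at the first failure.
3. Report other visits and the other VAS rating as estimates with confidence intervals and no claim of significance.
4. State whether these tests are for superiority or for the non-inferiority named in 2.9, and match the interval level to that choice. If non-inferiority is meant, the contrast must be one to which a margin can be applied.
5. Let the sponsor choose the visit after reconciling the 4-week intervention (section 2, Method/design, and 2.12) with the 6 months of Daoyin in 2.3. Week 4 cannot simply be taken as the end of treatment in both arms while these passages conflict. Reconcile the week 1 visit in 2.13 with 2.12 at the same time.

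**Cost.** Wording only, with no change in patients or visits. The downside is that later outcomes cannot be claimed if an earlier one fails. If Holm is preferred, the first step is tested at 0.05/3 = 0.0167. For a two-sided t test with 80% power, the detectable difference at that step rises from 0.74 to 0.86 SD at 30 evaluable per arm (the figure in 2.9 before the 20% loss allowance), or from 0.67 to 0.78 SD at the full 36.

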### Sample size calculation

2.9

We estimated the sample size based on the main outcome indicators, and we conducted a randomized trial of Shi-style lumbar spine manipulation combined with Daoyin therapy versus lumbar traction from March to September 2018, with 10 participants in each group. The outcome parameter was the rate of improvement in the NDI (neck disability index) score from baseline to the end of the 8-week treatment. The results showed that the rate of improvement after Shi-based lumbar spine manipulation combined with Daoyin therapy was 92.0%, while that after lumbar traction was 86.6% (*P* = .893) (α = 0.05, test efficiency 1 − β = 0.8, and equivalent standard δ = 0.2).

Because our study protocol will involve the use of a non-inferiority test, according to the number of cases in the clinical non-inferiority and equivalent tests and the equivalent standard,^[17]^ and using counting data (rates) as the outcome indicators, the following formula was used to estimate the number of patients required for this study:$$n=2\times {\left({\text{U}}_{\alpha }+{\text{U}}_{\beta }\right)}^{2}\times \text{p}(1-\text{p})/\delta^{2}$$

2 × (U_α_+ U_β_)^2^was calculated as 12.365, and N was 29.537 after substituting the above figures, and the sample size of each group was about 30 cases; according to the loss rate of 20%, the sample size of each group was 36 cases, and the ratio of treatment group and control group was 1:1, a total of 72 cases.

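### Pressure pain threshold, one of three primary outcomes, is defined at the neck in a trial of lumbar disc herniation

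*Protocol article*

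**What the plan says.** Section 2.7.1 (Primary outcome measures) describes three measures in turn. On the VAS it states: "we chose the VAS score as one of the primary outcome measures for evaluating low back and leg pain". It continues: "The pressure pain threshold (PPT) will also be measured". It then names the ODI as the last of the primary outcomes. PPT is therefore a primary outcome, one of three.

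The same section treats PPT as an inverse measure of pain severity: the worse the pain, the lower the threshold. It fixes the site in one sentence, under which "a hand-held pain meter will be used to measure the PPT in the painful area of the neck". The patient lies prone.

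The Abstract and section 2.13 (Statistical analyses) also mention PPT, and section 2.12 gives the timing of the primary outcomes. None of them names a measurement site, so the neck is the only site in the document.

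**The concern.** The site belongs to a different part of the spine from everything else in the trial. PPT depends on where the meter is pressed. It reflects the pain under study only if it is taken where that pain is.

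Two things are at stake. First, an assessor who follows the text literally records a primary outcome in a region that is neither the site of the disease nor a stated target of treatment. A patient without neck pain gives that assessor no valid place to measure. Second, assessors who notice the conflict may settle it in different ways. Section 2.1.2 refers to sub-centers and the Discussion calls the study multicenter, so more than one team may be reading this sentence. Neck and lumbar thresholds could then end up in the same variable.

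**Working it through.** The point is textual, so the check sets the statements side by side.

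| Element | Where | Region |
|---|---|---|
| Condition enrolled | 2.1.1 | Lumbar disc herniation; no neck pain criterion |
| Experimental arm | 2.3 | Lumbar: "The patients in the treatment group will undergo Shi-style lumbar manipulation for 20 minutes every other day (3 times a week) for 4 weeks" |
| Manipulation steps | 2.4 | Waist, back, hips, thighs, calves |
| Daoyin exercises | 2.5 | Trunk, hips and legs; neck and head appear only as positions to hold |
| Control arm | 2.6 | Lumbar/pelvic: "Patients with pelvic traction lie supine on the traction bed" |
| VAS | 2.7.1 | Low back and leg |
| Imaging outcomes | 2.7.2 | Spine and pelvis alignment, lumbar muscle |
| **PPT** | **2.7.1** | **Neck** |

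**Can the sentence be read as lumbar?** No. The neck is named outright. The prone position does not decide the matter, because it suits the back of the neck as well as the low back.

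**Can every eligible patient be measured as written?** Not necessarily. The sentence presupposes a painful neck area, and sections 2.1.1 and 2.1.2 do not require one.

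**Extent.** Section 2.12 sets 5 assessments of the primary outcomes, and section 2.9 sets 72 patients: 72 × 5 = 360 planned PPT readings fall under this definition. (Section 2.13 adds week 1 to the list of time points; that is a separate discrepancy.)

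**Does the sample size depend on PPT?** The figure in section 2.9 reproduces without it:

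- One-sided α = 0.05 and power 0.80 give 2 × (1.645 + 0.842)² ≈ 12.365.
- p = (0.920 + 0.866) / 2 = 0.893, so p(1 − p) = 0.893 × 0.107 = 0.095551.
- n = 12.365 × 0.095551 / 0.2² = 29.537, or 30 per group.
- The plan's allowance for loss is 30 × 1.2 = 36 per group, 72 in total.

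PPT does not enter this calculation, so correcting the site changes no figure in it.

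**Interaction with missing data.** Section 2.13 carries the last observed value forward for all measures. A neck value carried into a series of lumbar values would mix two sites within one patient. Simply declaring neck values missing does not solve this: a missing baseline has no earlier value to carry, and that patient loses the change from baseline.

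**The case against.** The strongest reply is that this is one wrong word in a condensed article. The rest of section 2.7.1 concerns lumbar disc herniation, and the case report form and assessor instructions, which are not shown, may well name a lumbar site. Section 2.1.2 says that recruitment is ongoing, but not that assessors work from this sentence. That stands: the document shows a contradiction in the definition and does not show a mis-measured outcome. It does not remove the point. Condensing explains an omission, whereas this is a positive statement of the wrong site. If assessors do measure the low back, the published definition of a primary outcome differs from practice and still needs correcting.

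A reader might also infer more than the text supports:

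- **That the disability outcome is compromised too.** Section 2.9 reports a pilot whose outcome was the "rate of improvement in the NDI (neck disability index) score". This makes carried-over neck-trial text a fair guess, but it describes the pilot behind the sample size and is a separate matter. The outcome of this trial is named throughout as the ODI.
- **That the wrong questionnaire is in use.** Section 2.7.1 says: "The ODI consists of 2 parts and a total of 10 evaluation items". It then names 3 symptom and 6 activity items, 9 in all. The list stands in parentheses and is not said to be complete, so it does not show a wrong form.
- **That the treatment effect shrinks by a known amount.** One could argue that if a fraction f of readings is at the neck, only (1 − f) of the lumbar effect remains. That assumes no effect at the neck, and f is unknown. The document gives no PPT effect or standard deviation.
- **That many patients lack a painful neck area.** No prevalence is given; only that some may.

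**Conclusion.** The PPT definition is wrong as written and must be corrected. It contradicts the population, both treatments and the pain that the trial targets, and nothing elsewhere in the article puts it right. Its extent is one of three primary outcomes and all 360 planned PPT readings.

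The conclusion rests only on the text of sections 2.1 to 2.7. It makes no assumption about what assessors have done, and the size of any bias cannot be computed from the document. The sample size, VAS and ODI are not shown to be affected.

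**What to change.** 1. Amend section 2.7.1 to name one lumbar measurement site for PPT, fixed for each patient at baseline and re-used at every later visit.
2. Check the case report form and the assessor instructions, at every participating site, for the location actually used.
3. If any readings were taken at the neck, identify them and do not pool them with lumbar readings in the PPT analysis. Decide how they are handled before treatment codes are released to the analysts, and report that decision. Do not carry a neck value forward into a lumbar series.

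The text change and the check are cheap. The possible cost is in data: patients whose baseline was taken at the neck have no usable lumbar baseline, so some PPT data already collected may be lost. That loss should be reported openly, not filled in.
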